### Impact analysis

For the second objective of assessing the overall community impact of the intervention, its acceptability, adoption, implementation and maintenance will be explored at the individual, community and organisational level. For this purpose, a systematic analysis will be performed based on the RE-AIM evaluation framework and its proposed dimensions ((1) Reach, (2) Efficacy, (3) Adoption, (4) Implementation and (5) Maintenance).^50^ Each dimension will be analysed separately, using pieces of data collected by the above-mentioned methods and as described in table 2, and results will be expressed as percentages. Ultimately, the combination of all five dimensions will result in a score that Glasgow and colleagues refer to as «public health impact» or «population-based effect».^50^

**Table 2 T2:** Impact analysis evaluation based on the RE-AIM framework

Dimensions	Social level	Evaluation criteria
Reach Proportion of the target population that has participated in the intervention	Individual: Children Educators	Number and characteristics of children who: Have received at least half the planned lessons, as reported by the educators. Number and characteristics of educators who: Have received the health risk assessment. Have attended at least one face-to-face coaching session.
Efficacy Success rate of the intervention in reducing risk factors	Individual: Children Educators	Changes in: Anthropometric measurements. Clinical parameters. Quality of life.
Adoption Proportion of settings that has incorporated the intervention	Organisational: School educators School principals	Number and characteristics of: Schools that implemented the intervention. Health-promoting activities per school.
	Community: School educators Parents	Number and characteristics of: Educators who have adopted *KaziHealth* recommendations. Parents aware of and supporting *KaziKidz* activities.
Implementation Extent to which the intervention has been embedded in the schools under naturalistic conditions	Organisational: School principals	Number of: Grades and classes participating in the intervention. Terms per school year in which the intervention is being taught. Staff involved in delivering the intervention.
Maintenance Adherence to and dissemination of the intervention	Individual: Children Educators	Changes in: Physical activity and dietary behaviour.
	Organisational: Eastern Cape Department of Education Nelson Mandela University	Number and characteristics of: Schools/districts that have the intervention integrated into the curriculum/environment. Actions taken towards its permanent integration (policy), for example, teaching agenda of future educators.

RE-AIM, Reach, Efficacy, Adoption, Implementation, Maintenance.

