### Study population

Originally, in the *KaziBantu* project, both *KaziKidz* and *KaziHealth* interventions were conducted in four schools, whereas the other four participating schools were used as controls.^30^ In total, 975 children from fourth to sixth grade (aged 8–16 years) were enrolled in the study; 482 children were allocated to the intervention and 493 to the control arm. At the same time, 160 educators were enrolled among all participating schools; of those, 85 took part in *KaziHealth,* whereas 75 served as waiting-list controls.

This study will follow up children and educators from the *KaziBantu* trial. While all educators who took part in *KaziHealth* have been invited to participate in this follow-up phase, a cohort of children from the *KaziKidz* intervention, who have been identified as having an increased risk for NCDs, have been included in this study. We have defined increased risk as a child presenting at least one of the following cardiometabolic risk factors: (1) overweight or obesity, (2) elevated blood pressure or hypertension, (3) pre-diabetes or diabetes, (4) borderline or dyslipidaemia; according to age appropriate, standard classifications (table 1) and based on *KaziBantu* baseline data from July 2019. Of the 975 children who participated in *KaziKidz*, 544 were classified as «high risk» according to the above-mentioned definition. Since then, 183 children have graduated from primary school resulting in 361 eligible learners. Of those, 240 have consented to participate and have been enrolled in this follow-up study at the time this protocol was published. Of the 160 educators enrolled in the *KaziHealth* program in 2019, 105 have consented to participate and have been enrolled in this study so far.

**Table 1 T1:** Classification criteria for cardiometabolic risk in children

Risk factor	Indicators and cut-off points
Adiposity^59 60^	BMI-for-age (SD)
Overweight	>+1 and ≤+2
Obesity	>+2
Blood pressure^61 62^	SBP and/or DBP (percentiles and mm Hg)
Elevated blood pressure	≥90th and <95th or <90th but ≥120/80
Hypertension stage 1	≥95th and ≤99th or ≥130/80
Hypertension stage 2	>99th or ≥140/90
Glycaemia^63^	HbA1c (mmol/mol)
Pre-diabetes	>39 and <48
Diabetes	≥48
Dyslipidaemia^64 65^	TC (mmol/l)
Borderline	≥4.40 and 5.15
Dyslipidaemia	≥5.15

BMI, body mass index; DBP, diastolic blood pressure; HbA1c, glycated haemoglobin; SBP, systolic blood pressure; TC, total cholesterol.

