Objective measurement of physical behaviours: PA will be measured for each participant using an accelerometer (ActiGraph wGT3X-BT, Pensacola, Florida, USA) which will be worn around the hip, at all times, for 7 days (five weekdays and two weekend days), except for activities involving water contact.

Questionnaires: Information on PA during school hours and in their free time will be self-reported by children using adjusted questions from the PA Questionnaire for Children.^38^ Dietary behaviours and nutrition will be self-reported by children through a tailored, validated food frequency questionnaire^39 40^ and by educators via a 24-hour dietary recall questionnaire.^41^ The validated KIDSCREEN-10 questionnaire, European generic health-related quality-of-life questionnaire (10-domain version), will be implemented to determine children’s physical and psychological well-being.^42 43^ Where necessary, questionnaires will be translated into the home language of the children, isiXhosa or Afrikaans, and additionally explained orally by students of the Nelson Mandela University. Self-reported psychosocial health in educators will be assessed through general perceived stress (four-item Perceived Stress Scale),^44^ work-related stress (Effort-Reward Imbalance),^45^ work and family conflict (Work and Family Conflict Scale),^46^ and burn-out symptoms (Shirom-Melamed Burnout Measure^47^) questionnaires. Information about educators’ work attendance will be obtained from the schools’ attendance registers. A self-developed questionnaire will be used to assess the continuity and extent of *KaziKidz*’s implementation in the schools and will be answered by the school representative.

The support for, and integration into the school curriculum of, *KaziKidz* and *KaziHealth* sustainability will be studied by qualitative research, employing credibility, transferability, dependability, confirmability and authenticity as quality criteria when employing qualitative methods.^48^

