### Longitudinal analysis

Mixed linear regression: Associations between longitudinal changes in continuous variables (eg, BMI) and individual characteristics, like sex and SES, will be assessed with random intercepts for schools and classes. Longitudinal changes in these outcomes will also be compared between the previous intervention and control schools after adjustment for personal characteristics. Moreover, changes in health parameters will be regressed against changes in PA and nutritional parameters. All analyses will be conducted, with and without adjustment, for the postintervention values of the respective outcomes. Also, potential associations between adjusted school-specific means of longitudinal changes in health parameters and the retrospectively assessed degrees of implementation of intervention measures in the respective schools will be assessed.

Mixed logistic regression: Longitudinal changes in categorical outcomes will be analysed by dichotomising polytomous outcomes. Analyses will be stratified according to the postintervention value of the dichotomised outcome, using mixed logistic regression models of the follow-up outcome with the same random effects structure and the same predictor variables, as previously described, for the mixed linear models. Additional analyses will be conducted by treating the postintervention and the two consequent FU outcomes as repeated measures.

To adjust for biases associated with missing data and/or lost to follow-up, inverse probability weighting will be used. Data imputation will be considered as an additional option if the drop-out rate is moderate (ie, <20%).

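### The RE-AIM Efficacy row calls change, with no comparator or reference reading, the intervention's success rate, in children selected for high values

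*Protocol article*

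**What the plan says.** Protocol article, Impact analysis and Table 2: the Efficacy dimension is "Success rate of the intervention in reducing risk factors", at the individual level for children and educators. The evaluation criterion is "Changes in: Anthropometric measurements. Clinical parameters. Quality of life". For every dimension, "results will be expressed as percentages", and "the combination of all five dimensions will result in a score" read as the public health impact.

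Study population: "We have defined increased risk as a child presenting at least one of the following cardiometabolic risk factors", judged on "baseline data from July 2019". All educators were invited, whatever their risk.

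Intervention: after 2019 all eight schools were free to run both programmes. Study design: the cohort has no followed control group, and participants from schools that decline the programme would serve as comparison.

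Longitudinal analysis: changes are nevertheless to be compared between former intervention and former control schools, adjusted for personal characteristics. School-level changes are also to be related to the degree of implementation. Table 2 refers to neither analysis.

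Data collection: "Self-reported psychosocial health in educators will be assessed through general perceived stress", together with effort-reward, work-family conflict and burn-out scales. KIDSCREEN-10 is assigned to children only.

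**The concern.** A success rate credited to an intervention needs a statement of what would have happened without it. The Efficacy row gives none. For children, selection on a high reading makes later readings lower on average, so part of any improvement is regression to the mean. The article does not mention this anywhere. For children and educators alike, the period between readings includes the pandemic and ordinary time trends. Children also grow, which matters for any measure not standardised for age. Regression to the mean flatters the programme; the other influences can work in either direction. The resulting percentage enters a score that the article presents as evidence for policy.

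The row also lists quality of life for educators, but the article describes no quality-of-life instrument for them.

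**Working it through.** **Inputs from the article:** 975 children (482 intervention + 493 control), 544 classified high risk, 183 graduated, 240 enrolled so far. **Assumed, not in the article:** four independent risk factors of equal prevalence, normal readings, retest correlation r from 0.6 to 0.95, zero programme effect, no time trend.

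**1. The article's own figure.** 544 − 183 = 361 eligible children, which reproduces. Since 482 + 493 = 975, the 544 come from a pool containing both arms.

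**2. Calibration.** The share with at least one factor is 544/975 = 0.558. With four independent factors, each has prevalence p = 1 − (1 − 0.558)^(1/4) = 0.185.

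**3. One factor, change from the selecting reading.** With cut-off c, the expected change is −(1 − r) × φ(c)/p, where φ(c)/p ≈ 1.44. At r = 0.6 this is −0.4 × 1.44 = −0.58 SD; at r = 0.95 it is −0.05 × 1.44 = −0.07 SD. Let q be the probability of being below the cut-off at retest, given above it at selection. By simulation, q is 0.518 at r = 0.6 and 0.182 at r = 0.95.

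**4. Clearing all four factors.** The probability of being below one cut-off both times is (1 − p) − p·q. Hence

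P(no factor at follow-up | at least one at selection) = {(1 − p)^4 − [(1 − p) − p·q]^4} / 0.558.

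- r = 0.6: (0.442 − 0.720^4)/0.558 = (0.442 − 0.268)/0.558 = 0.31
- r = 0.95: (0.442 − 0.782^4)/0.558 = (0.442 − 0.374)/0.558 = 0.12

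Simulation agrees and fills in the range:

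| r | Cleared all | Of 240 | Fewer factors | More factors |
|---|---|---|---|---|
| 0.6 | 31% | 74 | 45% | 14% |
| 0.7 | 28% | 66 | 41% | 13% |
| 0.8 | 23% | 55 | 36% | 13% |
| 0.9 | 17% | 40 | 28% | 11% |
| 0.95 | 12% | 29 | 21% | 8% |

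In the same simulation, prevalence in the whole unselected cohort stays at 56%. Nothing has changed except who was selected.

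**5. Change from the postintervention reading.** If the correlation does not depend on the interval, the expected change is about 0. If it decays by a further factor d, the expected change is −(1 − d) × r × 1.44. With d = 0.9 and r = 0.7 this is −0.10 SD; with d = 0.8 and r = 0.9 it is −0.26 SD.

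**6. A contrast.** Two groups selected by the same rule regress by the same expected amount, so the expected difference in change is 0 under this model.

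**The case against.** The strongest reply is that Table 2 lists data domains and not estimators, and that the section just before it plans the adjusted comparison of former intervention and control schools. This stands in part. A reader might infer that the plan contains no controlled comparison of change; that would be wrong. What remains is that the Efficacy row is not tied to that comparison, while its definition attributes the result to the intervention.

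A second reply is that the longitudinal models adjust for, or stratify by, the postintervention value, from which the selection artefact is small. This also stands, but Table 2 does not name that reading as its reference.

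A reader might also infer three larger problems that the article does not support:

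- **A larger artefact.** Single-factor rates run higher (52% at r = 0.6 and 18% at r = 0.95 for the calibrated prevalence). They apply to one factor measured from the selecting reading and are not the size of the problem for the row as a whole.
- **Efficacy scored on raw BMI.** The article cites BMI as an example when describing "Associations between longitudinal changes in continuous variables (eg, BMI) and individual characteristics, like sex and SES", but those models are not limited to children. Table 1 already defines child adiposity and blood-pressure risk on age-standardised scales. Table 2 merely does not say that it uses them.
- **Selection bias among educators.** Educators were not chosen on risk. For them the issue is the missing comparator and time trend.

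The quality-of-life entry may have been meant for children alone, since one cell serves both groups. It is a wording gap.

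**Conclusion.** The point holds in limited form. As written, the Efficacy row credits uncontrolled change to the intervention and passes it to the impact score. Under zero effect, selection alone would show about 12% to 31% of the children clearing all risk factors from the July 2019 reading (29 to 74 of the 240 enrolled). From the postintervention reading the artefact is about 0, or 0.10 to 0.26 SD if correlation decays with time. These figures rest on assumed retest correlations, independent factors of equal prevalence and normality; the article supplies only 544/975. Time and pandemic trends come on top, for children and educators, with unknown sign, so the net direction of bias cannot be stated. The description of the row as uncontrolled is itself inferred from its silence on a comparator.

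**What to change.** 1. Define Efficacy as the adjusted difference in change between former intervention and former control schools, as already planned under Longitudinal analysis, with a confidence interval. For risk-factor status it can still be given in percentage points.
2. Name the reference reading.
3. Label the result as the effect of original allocation. All eight schools could run the programmes after 2019, so it does not estimate the effect of continued exposure. Report the planned association with degree of implementation beside it.
4. For children, use the BMI-for-age and blood-pressure percentile scales of Table 1.
5. For educators, name the perceived-stress, effort-reward, work-family conflict and burn-out scales in place of quality of life.
6. If no contrast is used, call the row uncontrolled change and do not describe it as the intervention's success rate.

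The cost is wording only, since the assessments are already planned. The price is precision: with four schools on each side, the efficacy estimate will be less precise than a simple percentage of children who improved.

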### Participant and public involvement

Adult participants were involved in the conception of the research question by identifying their pivotal role in both the implementation and maintenance of the intervention. They will collaborate in the methodology via interviews and FGDs, where preliminary results will be presented for their verification. Participants will also contribute to the results by reporting on the burden of the interventions and specific local needs.

Participants have been informed on the study, alongside their right to voluntary participation and withdrawal at any time without justification. Before taking part in any assessment, as proposed by this study, oral assent has been sought from children and written consent from their guardians, as well as from the participating educators.

Study results will be summarised in manuscripts and submitted for publication to open-access, peer-reviewed scientific journals. Results will also be presented at relevant national and international conferences and workshops.

### Methodological limitations

The implementation of *KaziKidz* and *KaziHealth* will not be monitored by the research team and schools were given the freedom to decide whether, and to what extent, they will deliver the health interventions. Therefore, any participating school may decide not to implement the interventions after completion of the *KaziBantu* trial. The extent of *KaziKidz*’s implementation will be assessed via questionnaire with school representatives and information about the reasons for discontinuation will be sought; this information will be considered for the feasibility assessment. Similarly, the status and extent, including reasons for discontinuation, of *KaziHealth*’s implementation will also be explored and evaluated via FGDs with school educators, headmasters’ and ECDoE officials. Furthermore, for those cases where a further implementation of the interventions has not taken place, it will be aimed at measuring the corresponding children and educators at the foreseen follow-up time points.

### Discussion

Globally, a total of 41 million deaths are attributable to non-communicable, chronic conditions, such as diabetes, coronary heart diseases or cancer every year. Of those deaths, it is estimated that around 80% are preventable because they are associated with poor diets, physical inactivity, alcohol addiction, tobacco use and polluted environments. However, NCD aetiology is very complex and individuals cannot be held responsible because they live in a system that encourages unhealthy behaviours. Hence, aiming merely to change behaviours might be complicated and ineffective over time. Instead, the focus should be on tailoring interventions aimed at creating environments that promote healthy lifestyles, making the system more beneficial, accessible and affordable for everyone. This is especially important in the early stages of life, where healthy behaviours can be adopted naturally and maintained throughout life. Furthermore, NCDs are a major threat to individual and national economic development: unhealthy habits acquired during childhood will most likely lead to unhealthy adults who are unable to develop to their full potential.^51^

The COVID-19 pandemic has highlighted the increased risk for severe disease and mortality faced by people living with chronic conditions.^52^ At the same time, it has jeopardised the livelihood of millions of families, disproportionately hitting the most vulnerable and taking a special toll on children.^53^ By December 2020, South African children lost up to a third of the school year, thus, not being able to complete the entire curriculum and leaving many gaps in children’s education. Moreover, socioeconomic inequality is also likely to have further increased, since poorer learners and schools were least able to catch up.^54^

On reopening in both 2020 and 2021, schools in South Africa have been forced to adopt strict measures to further limit the spread of COVID-19. In addition to the staggered return to the school system, the 1.5 m social distancing requirement has led to schools incorporating what they referred to as a block teaching system, whereby schools operate at 50% or less of their capacity. More information on COVID-19-related school lockdown and closure in South Africa and the Gqeberha region can be found in online supplemental material. Furthermore, the ECDoE advised schools not to exclude any of the subjects from the curriculum, but to prioritise the more heavily weighted academic subjects, such as English, Afrikaans, Mathematics and Science. Physical education is currently not a stand-alone subject in the South African curriculum but forms part of the Life Orientation/Life Skills subject. Consequently, the likelihood of physical education receiving limited attention, and even being neglected, throughout the COVID-19 pandemic is high. Hence, we believe that the implementation of the *KaziKidz* material might have been affected too, which justifies further exploration. The complexity of lifestyle interventions, such as *KaziKidz* and *KaziHealth,* and their successful implementation reside in their multidimensional nature, that is, the involvement of individual, environmental and policy factors that interact at multiple social levels (individual, community and organisational institutional). The RE-AIM framework will be followed to predict the feasibility of both interventions in terms of effectiveness, addressing whole populations, being long-lasting and becoming institutionalised.^50 55 56^ The information obtained from linking the intervention integration level in the schools with the personal adoption of behavioural changes and the achieved health effects both in children and educators, will yield unprecedented results on lifestyle interventions’ potential to effectively promote the acquisition and maintenance of healthy lifestyles during childhood and adulthood that will ultimately support overall community health and well-being. Furthermore, we believe that continuing with the assessments indicated in the methodology sections will provide valuable insights into the children’s health amidst the COVID-19 pandemic, and facilitate contextually valid recommendations for future interventions, policy and practice.

10.1136/bmjopen-2020-047296.supp1Supplementary data

Finally, due to the multifactorial nature of NCDs, collaboration among different sectors, such as governments, communities, academia and the private sector, is necessary. The comprehensive evaluation of a tailored school-based health promotion intervention presented in this paper could provide unique evidence and support the dissemination of the intervention and collaboration between partners from different sectors,^57^ ultimately influencing local policy.^58^

